### Micro-level hypotheses

H1. Group singing may lead to increases in positive mood—more so than the participants in the control group.H2. Group singing may foster greater feelings of social closeness—more so than the participants in the control group.

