#### Micro timepoint testing

The purpose of the micro timepoint testing is two-fold. Firstly, to examine the physiological and psychosocial changes that occur from *pre-* to *post-session*; and secondly, to examine the cumulative longitudinal impacts on physiological measures for each intervention. Micro timepoint testing consists of HRV and the following questionnaires presented in fixed order: PANAS, IOS, SUDS.

The micro timepoint testing will occur on-site where the training occurs at: 1) Pre-session (directly before the intervention begins); and 2) Post-session (directly after intervention ends). Testing will involve biophysical measures and questionnaires (described in detail under the Test Battery and Test Procedure sections). These micro measures will be taken at the training sessions in Week 2, 7, and 11 and designed to be indicative of pre- and post-session measures corresponding to the start, middle, and end of the training program.

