#### Difference score and outlier rejection

Outliers due to technical errors will be removed. Univariate outliers on continuous independent and dependent variables will be rejected based on a boxplot method, wherein a data point is an outlier if it falls 1.5 times outside of the interquartile range. Because each group may have unique distributions, we plan to reject outliers based for each group individually. For each of the micro-level dependent measures, a difference score will be computed (i.e., *pre-* to *post-session*).

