For each micro-level dependent variable, three separate MLMs will be defined: 1) an intercept-only model; 2) a main-effect only model (DV_change_ ~ *group + time*) and 3) an interaction (DV_change_ ~ *group * time*) model. For micro-level models, the time variable will reflect the time point of the micro-level observation and will allow us to model changes between the group across time. Similarly, three separate MLMs will be defined for macro-level dependent variables: 1) an intercept-only model; 2) a main-effect only model (DV ~ *group + session*) and 3) an interaction (DV ~ *group * session*) model. For both macro and micro-level models we will use a hierarchical modeling technique to determine which model is the best fit to the data. Model fit parameters will be compared between the three models and results of the model with the best fit will be reported on. Upon the discovery of a significant interaction, a follow-up simple slope analysis will be used to examine the differences in time (e.g., *baseline* vs. *completion*) across groups. For all hypothesis tests, alpha values will be set at 0.05.

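### For the micro outcomes, once the interaction model is selected, no stated contrast answers whether singing's session gain exceeds the control's (micro H1 and H2)

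*Protocol article*

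**What the plan says.** Both micro hypotheses compare the arms. H1: "Group singing may lead to increases in positive mood—more so than the participants in the control group". H2: "Group singing may foster greater feelings of social closeness—more so than the participants in the control group".

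Under Difference score and outlier rejection: "For each of the micro-level dependent measures, a difference score will be computed", taken from before to after the session. On timing, Micro timepoint testing says: "These micro measures will be taken at the training sessions in Week 2, 7, and 11". Modelling and inferential statistics defines the time factor accordingly: "For micro-level models, the time variable will reflect the time point of the micro-level observation".

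Three models are planned for each micro outcome: intercept only, `DV_change ~ group + time`, and `DV_change ~ group * time`. Their fit is compared and only the best-fitting one is reported; the fit criterion is not named. A single follow-up rule serves macro and micro outcomes alike: "Upon the discovery of a significant interaction, a follow-up simple slope analysis will be used to examine the differences in time", across groups. Its only worked example is baseline against completion, which is a macro comparison.

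**The concern.** In the macro models the outcome is a raw score, so group by session is the treatment effect and simple slopes over session are a natural follow-up. In the micro models the before/after difference has already been taken. The group term on the change score therefore carries H1 and H2, while group by time asks whether that arm difference drifts over the weeks. These are separate questions, and the article applies one selection and follow-up rule to both model families.

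As a result, the quantity reported for H1 and H2 depends on which model wins. If the main-effect model wins, its group term is the right test. If the interaction model wins, the planned output is a set of time slopes by arm plus a group coefficient whose meaning depends on how time is coded. The only two stated micro hypotheses could then be decided by an unintended quantity, or left to a choice made after the data are seen.

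**Working it through.** **No figure in the plan to reproduce.** The power analysis (N = 206) concerns the macro interaction on speech-in-noise perception. The article gives no effect size, correlation or power for the micro outcomes.

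**Inputs.** From the article: 210 participants, 1:1 allocation, 20% attrition, Weeks 2, 7 and 11, alpha 0.05 (taken as two-sided). 210 × 0.8 = 168, or 84 per arm. Assumed: change scores with SD 1, within-person correlation ρ of 0.3 to 0.5, the effect sizes below, time entered as week number or as a factor with Week 2 as reference, selection by likelihood ratio at 0.05 or by AIC, and no clustering by choir or site.

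**What each term estimates.** Let d2, d7 and d11 be the arm differences in session gain.
- H1/H2 contrast: (d2 + d7 + d11)/3.
- Group by time: null when d2 = d7 = d11, whatever their common value.
- Group coefficient in the interaction model: d2 if time is a factor, or the fitted difference extrapolated to Week 0 if weeks are entered as numbers.
- Simple slopes: drift of the gain within each arm.

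**Direct contrast.** SE = √[(2/84)(1 + 2ρ)/3], which is 0.113 at ρ = 0.3 and 0.126 at ρ = 0.5.
- Constant 0.30 SD: 0.30/0.113 = 2.66, power Φ(2.66 − 1.96) = 76%; 0.30/0.126 = 2.38, power Φ(0.42) = 66%.
- Growing 0.2/0.4/0.6 SD (mean 0.40): 3.55 gives 94%; 3.17 gives 89%.

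**Group coefficient in the interaction model, growing benefit.**
- Factor time: the target is d2 = 0.2 and SE = √(2/84) = 0.154. 0.2/0.154 = 1.30, power Φ(−0.66) = 25%.
- Numeric time: the mean week is 6.67 and the squared deviations sum to 40.67. Slope = (4.67 × 0.2 + 4.33 × 0.2)/40.67 = 0.0443 per week, so the value at Week 0 is 0.40 − 0.0443 × 6.67 = 0.105 SD. SE = √{(2/84)[(1 + 2ρ)/3 + (1 − ρ) × 6.67²/40.67]}, which is 0.176 or 0.170. Power is about 9%.

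These are unconditional powers within that one model. The planned procedure mixes them with runs where the main-effect model is chosen, so simulation is needed.

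**Simulation of the whole select-then-report rule** (ranges over ρ, coding and criterion):

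| Benefit at Weeks 2/7/11 (SD) | Direct contrast significant | Favourable group term in the reported model | Loss |
|---|---|---|---|
| 0.30/0.30/0.30 | 65-76% | 46-69% | about 5-20 points |
| 0.2/0.4/0.6 | 87-95% | 16-52% | about 40-75 points |
| 0.7/0.45/0.2 | 94-98% | 99-100% | none |

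In the second row the interaction model is chosen in 47-88% of runs. In the third it is chosen in 70-97%, and the singing slope is significantly negative in 69-97% of all runs, although singing is better at every week. In the first row much of the loss arises because the comparison with the intercept-only model tests group and time jointly.

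**The case against.** The strongest reply is that the H1/H2 test is already planned: the group term of `DV_change ~ group + time` is exactly the averaged arm difference. With a steady benefit that model usually wins and is reported. This stands, and it rules out three stronger readings that a reader might infer.

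- *The interaction is the planned test of H1/H2.* The article never says so.
- *A steady benefit would be found only about 5% of the time.* That is the rate at which the interaction is significant when the benefit is constant. The benefit is found through the selected model in 46-69% of runs.
- *A shrinking benefit would be reported as evidence against singing.* Under the assumed coding the group coefficient sits where the benefit is largest and is almost always favourable. The risk is confined to misreading the negative slope from the follow-up.

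It can also be said that coding and marginal means are details for an analysis plan that is not shown, that drift over weeks is a legitimate question, and that with a growing benefit the slopes would favour singing and draw attention. All fair. But the point does not rest on missing detail. The article states a rule (report one model, then follow up on time), and under that rule no stated contrast addresses H1/H2 when the interaction model is selected. A slope that favours singing still does not show that singing's gain exceeds the control's.

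**Conclusion.** The point holds in this limited form. The main-effect model tests micro H1 and H2 properly, but its result is reported only if that model fits best. When the interaction model is selected, the stated follow-up answers a question about drift and nothing stated answers H1/H2. This structural conclusion follows from the definitions of the outcome and of time, and needs no assumed numbers.

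The size does depend on assumptions. The cost is modest for a constant benefit (roughly 5 to 20 points of power at 0.30 SD). It is large for a benefit that grows over the weeks (about 40 to 75 points at 0.2/0.4/0.6 SD), provided the group coefficient is read under default coding. For a shrinking benefit there is no loss of power, only a slope open to misreading. Effect sizes, correlation, coding and fit criterion are all assumed, and clustering was ignored. The trial was sized on a macro outcome, so this does not affect the sample size, but it bears on both stated micro hypotheses.

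**What to change.** In Modelling and inferential statistics, give the micro outcomes their own rule, for example:

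*Micro H1 and H2 are tested by the singing-minus-audiobook contrast on DV_change averaged over Weeks 2, 7 and 11, with time as a three-level factor, as a marginal mean difference with 95% CI. This contrast is reported whichever model fits best. Group by time is a secondary question about drift; if it is significant, the arm difference at each week is reported alongside any time slopes.*

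The cost is a few sentences and one contrast statement in R, with no new data or participants. The small downside is that an effect present at one week only is diluted in the averaged headline test; the by-week differences show it if the interaction is significant.

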
Hence, the role of music training for individuals with hearing loss has been explored with cautious optimism, with the possibility that music training may enhance SIN perception as well as psychosocial outcomes. However, a systematic review of studies that tested the hypothesis that music training can enhance speech understanding in people with hearing loss showed that most of the studies had flaws in their methodologies and design such as no (or an inappropriate) control group, lack of randomisation, failure to account for multiple comparisons, or inadequate limiting of participant or tester bias [59]. Additionally, the four studies with appropriate designs did not show any benefit to speech understanding [60–63].

The strongest evidence that group singing enhances SIN for older adults with hearing loss, was a study involving a choir-singing group and an age- and audiometrically-matched control group, which did not participate in any activities, over a 10-week period [64]. Both groups were carefully matched based on previous musical experience, quantified by the years of formal musical training, thereby enabling causal inferences that are typically unachievable in correlational or cross-sectional studies of musicians’ auditory capabilities. The choir participants exhibited significant improvements in SIN perception, pitch discrimination, and the robustness of the neural encoding of speech stimuli (frequency following response, FFR). The enhancement in SIN perception among choir participants was mediated by improved pitch discrimination, which was, in turn, predicted by the strength of the FFR. Although these results support the hypothesis that short-term participation in choir singing serves as an effective intervention for mitigating ARHL, reasonable concerns about participant bias may be raised due to the use of a self-selected choir group and a do-nothing control group.

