### Macro-level hypotheses

H1. Group singing may be associated with better music perception such as pitch, rhythm, timbre, and higher-level music skills—more so than participants in the control group.H2. Group singing may be associated with better speech perception such as speech-in-noise and emotional prosody—more so than participants in the control group.
The mechanism for speech perception enhancement may be due to improvements in music perception (i.e., pitch, rhythm, timbre, or higher-level music skills.)H3. Group singing may be associated with better psychosocial health—more so than participants in the control group.
The primary outcome of interest is the enhancement of quality of life and social connectedness.The secondary outcomes of interest are the reduced symptoms of depression and anxiety, and the enhancement of self-esteem.

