## Data analysis

### Statistical power analysis

An a priori power analysis was conducted to determine the sample size needed to detect the smallest effect size of interest. We determined the number of participants needed to detect the cross-level interaction of group (i.e., group singing vs. audiobook club) and time (i.e., *baseline* vs. *completion*) on SIN perception. The power analysis was conducted using traditional approaches where the resulting sample size refers to the level 2 clusters–in this case, the number of participants.

*G*Power* version 3.1.9.4 was used to conduct the analysis for an ANOVA within-between factor interaction [119]. For a conservative estimate, we assumed a small effect size of, η^2^ = .01, corresponding to an effect size of f = 0.1. We estimated the correlation among the repeated measures to be *r* = .62, based on a previous group-singing controlled trial that reported an intraclass correlation (ICC) of .62 [64]. Accounting for a 20% attrition rate [64], the power analysis (f = .10, *α* = .05, *r* = .62) suggests a total sample size of *N* = 206 participants, approximately *n* = 30 per site for 85% power.

In addition to the power analysis, we also calculated the reliability of our repeated measurements to assess for sufficient reliability for each participant based on [120] (1):

$$n_{min}=\frac{\rho (1-ICC)}{\left(1-\rho )(ICC\right)}$$
(1)

where *n* min is the number of time points and *ρ* is the population correlation across all the timepoints. Given our two timepoints and estimated ICC of .62, we have adequate-to-good reliability of our timepoints, *ρ* = .77.

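### Every outcome is tested at 0.05 without multiplicity control, and no single trial-wide primary outcome is fixed: the outcome used for sizing differs from those called primary

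*Protocol article*

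**What the plan says.** All points are from the Protocol article.

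- **Error rate.** Modelling and inferential statistics defines three models for each macro and each micro dependent variable and then states: "For all hypothesis tests, alpha values will be set at 0.05". No adjustment or gatekeeping across outcomes appears.
- **Sizing outcome.** Statistical power analysis: "We determined the number of participants needed to detect the cross-level interaction of group" and time, on speech-in-noise (SIN) perception.
- **Outcome called primary.** Macro-level hypotheses, under H3: "The primary outcome of interest is the enhancement of quality of life and social connectedness". Depression, anxiety and self-esteem are ranked secondary there. H1 (music perception) and H2 (speech perception) carry no such ranking.
- **Exploratory label.** Exploratory analyses gives it to heart rate variability (HRV) and individual differences only.
- **The authors' own standard.** Benefits of group singing lists, among the flaws of earlier music-training studies, "failure to account for multiple comparisons".

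**The concern.** A flat 0.05 over many outcomes gives each test its nominal error rate but leaves the trial as a whole uncontrolled. A clearly named primary outcome would limit the damage, because the trial's conclusion would rest on one test. Here the outcome with a sample size behind it is not called primary, and the outcomes called primary have no sample size behind them. After unblinding, a report could lead with speech perception because the trial was powered on it, or with quality of life or social connectedness because they were called primary. The text rules out neither.

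This is not detail left to a statistical analysis plan. The article fixes 0.05 for all hypothesis tests, so a later plan that adjusted would contradict it.

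**Working it through.** **1. The plan's own sample size.** Inputs from Statistical power analysis: "version 3.1.9.4 was used to conduct the analysis for an ANOVA within-between factor interaction"; f = 0.10; r = 0.62; alpha 0.05; 85% power; 20% attrition. With two groups and two times, the noncentrality is λ = f² × N × 2 / (1 − r), on 1 and N − 2 degrees of freedom.
- N = 174: λ = 0.01 × 174 × 2 / 0.38 = 9.16, power 85.3%.
- If f is taken from η² = 0.01 as √(0.01/0.99) = 0.1005, N = 172 suffices.
- Attrition: 172 × 1.2 = 206.4 and 174 × 1.2 = 208.8, so the stated 206 is reproduced.
- With 80% of the planned 210 retained (168), power is 84%.

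This calculation is for one test, on SIN perception, at 0.05.

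**2. Counting scores tied to a stated hypothesis** (Test battery; Macro timepoint testing; Macro-level and Micro-level hypotheses):

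| Hypothesis | Scores | Number |
|---|---|---|
| Macro H1 | FDL, BAT, SMRT, MINT | 4 |
| Macro H2 | CRM, EmoHI | 2 |
| Macro H3 | SF-12 Physical and Mental (2), SCS-R (1), HADS (2), CSES subscales (4) | 9 |
| Micro H1, H2 | PANAS positive, IOS | 2 |
| **Total** | | **17** |

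MINT counts once although three conditions are used. Left out are EMO-CheQ (named only in the list of macro questionnaires), HRV (exploratory), and PANAS negative and SUDS (tied to no stated hypothesis).

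**3. Chance of at least one false positive.** Assumptions: no true effects, one test per score. For independent two-sided tests it is 1 − 0.95^k. For results favouring singing only, it is 1 − 0.975^k, against a nominal 2.5%.
- k = 17, two-sided: 1 − 0.95^17 = 58%.
- k = 17, favouring singing: 1 − 0.975^17 = 35%.
- k = 3 (SF-12 Physical, SF-12 Mental, SCS-R), two-sided: 1 − 0.95^3 = 14%.

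The article gives no correlations between outcomes. For normal test statistics with an assumed common correlation, two-sided:

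| Correlation | 17 scores | 3 scores called primary |
|---|---|---|
| 0 | 58% | 14% |
| 0.3 | 49% | 14% |
| 0.5 | 39% | 13% |
| 0.7 | 27% | 11% |

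**4. Power if the psychosocial outcomes are primary.** Splitting alpha over three scores gives 0.05 / 3 = 0.0167. With 168 completers and the f and r above, power per score is about 71%. Reaching 85% takes 228 completers, or 228 / 0.8 = 285 enrolled.

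**The case against.** Several limits on the point stand.

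- **There is some ranking.** H3 separates primary from secondary outcomes, HRV is exploratory, and the mechanism analysis runs only after a significant speech result. It would be wrong to say that the plan has no hierarchy. None of these steps controls error across outcomes, however.
- **Primary may mean primary within H3.** On that reading the label does not contradict the sizing section, but then no trial-wide primary outcome is named at all.
- **The power basis is partly generic.** The effect size f = 0.10 is presented as the smallest of interest; only r and attrition come from an earlier singing trial. The same N would give similar per-test power for SF-12 or SCS-R if their repeated-measures correlation were similar. The article neither shows nor excludes this, so power for those outcomes is unjustified rather than shown to be wrong.
- **The hypotheses are directional.** Counting only errors in favour of singing lowers the independent figure from 58% to 35%.

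A reader might infer that a chance positive is more likely than not, or count all 21 macro and micro scores and quote 66%. The documents do not support either as a headline. A figure above 50% needs independence or weak correlation, which is doubtful among subscales of the same questionnaire, and the count of 21 includes scores tied to no stated hypothesis.

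**Conclusion.** The point holds on either reading of the word primary. The stated rule leaves false positives uncontrolled over about 17 hypothesis-linked scores. The two-sided chance of at least one is between 27% (correlation 0.7) and 58% (independence), roughly 5 to 12 times the nominal 5%. For the three scores called primary it is 11% to 14%. These figures assume no true effects, one test per score and a common correlation that the article does not supply.

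The mismatch between labels is a fact of the text and needs no assumption: no single outcome both carries the primary label and has a justified sample size. The article faults earlier studies for the same lack of multiplicity control.

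**What to change.** Reconcile Macro-level hypotheses, Statistical power analysis, and Modelling and inferential statistics before any results are seen.

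1. Name the group by session interaction on the CRM speech reception threshold as the single primary test at two-sided 0.05. This matches the sizing section and leaves its power unchanged.
2. If the sponsor prefers the psychosocial outcomes as primary, split alpha across them and restate the power, about 71% per score at 0.0167 with 168 completers under the article's assumptions, or raise the sample size.
3. Replace the flat 0.05 rule with Holm or false discovery rate control within the H1, H2, H3 and micro families.
4. Report the remaining outcomes (EMO-CheQ, PANAS negative, SUDS, HRV) as estimates with confidence intervals and no confirmatory claim.

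Control within families does not bound the error across them: with Holm, four independent families each at 0.05 still give 1 − 0.95^4 = 19%. The trial's main conclusion should therefore rest on the primary test.

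The cost is a change of wording in the protocol and analysis plan, with less power for the secondary outcomes and fewer of them called significant. Under option 1 no extra participants are needed.

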#### Mechanisms and contributions to speech perception

If a statistically significant benefit from group singing is found for speech perception, we will examine if changes in musical perception (i.e., FDL, BAT, and SMRT) are potential mechanisms or contributors for this change in speech perception (i.e., CRM and EmoHI). To do this, a hierarchical method will be used to compare a model which predicts speech perception difference score from BAT, FDL, and SMRT difference scores to a model which also contains an interaction term between speech perception variables and the group variable. The model which is a better fit for the SIN change scores will be reported on, and any significant interactions will be decomposed using simple slope analysis.

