The Music-in-Noise Task (MINT) will be used to measure inter-individual differences in hearing-in-noise skills [109]. MINT is utilized as a measure of higher-level musical skills. The MINT uses a match-mismatch trial design, whereby participants first listen to a short instrumental excerpt presented in “multi-music” noise, followed by either a matched or scrambled version of the excerpt presented in silence, and are asked to judge whether the two excerpts are the same. The MINT includes five listening conditions, of which we will utilize three (Baseline, Rhythm, and Prediction [reversed order]), which differ according to the presence or absence of different types of contextual cues, which have been shown to be differentially sensitive to musical and linguistic expertise [109]. The Baseline condition provides no additional cues. In the Rhythm condition, the tones of the instrumental excerpts are all the same pitch within each trial. As such, rhythmic variation between matched and mismatched pairs represents a form of rhythmic cueing. In the Prediction condition, the excerpts are presented in silence first, followed by the noise-masked pair. This predictive cueing helps to anticipate incoming information when the excerpt is presented in noise. Each MINT condition includes 20 trials, with four familiarization trials for each condition prior to the start of the main task. Difficulty is also varied by adjusting the signal-to noise ratio (SNR) between the musical excerpt and the background noise, such that musical excerpts will be more or less hidden in the background noise. Conditions will be tested at four different signal-to-noise levels (0, −3, −6, and −9 dB).

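### The mechanism analysis is mis-specified for the mediation question in H2: the outcome appears among the predictors, no indirect effect or group main effect is stated, and MINT is left out

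*Protocol article*

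**What the plan says.** Under H2, the protocol article (Macro-level hypotheses) proposes a chain: "The mechanism for speech perception enhancement may be due to improvements in music perception (i.e., pitch, rhythm, timbre, or higher-level music skills". Four music domains are named. Music perception materials assigns the fourth to a specific test: "MINT is utilized as a measure of higher-level musical skills". Macro timepoint testing lists MINT with the other behavioural tests given at baseline and completion, so a MINT change score will exist.

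The analysis is in the section Mechanisms and contributions to speech perception. It runs only if singing shows a significant benefit on speech perception, and it asks "if changes in musical perception (i.e., FDL, BAT, and SMRT) are potential mechanisms or contributors for this change in speech perception", naming CRM and EmoHI as the speech measures. Two models are compared:

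- Model 1: "compare a model which predicts speech perception difference score from BAT, FDL, and SMRT difference scores".
- Model 2: "a model which also contains an interaction term between speech perception variables and the group variable".

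The better-fitting model is reported and any significant interaction is decomposed by simple slopes. Group is mentioned only inside the interaction. The last sentence speaks of SIN change scores, which leaves EmoHI's place unclear.

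**The concern.** H2 asks whether singing improves music perception and whether that improvement carries over to speech. The planned comparison does not address this, for four reasons.

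1. The speech change score is the dependent variable, and the term added in model 2 is built from speech variables.
2. If music variables were meant, the added term is a test of effect modification. No indirect effect is estimated anywhere.
3. Model 1 states no group term. If singing shifts both music and speech scores, the two changes correlate across the pooled sample with no causal link between them.
4. The closed list of three music measures drops MINT, so one of the four pathways in H2 goes unexamined.

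At stake is how the mechanism result is read. A slope in model 1 could be reported as evidence of a mechanism when it reflects only that both scores responded to singing.

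**Working it through.** The section states no figure to reproduce. The check sets the models against H2 and then sizes the consequences.

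**Inputs.** From the protocol: 210 participants, 1:1 allocation, 20% attrition, f = 0.10, r = .62, alpha 0.05.
- Completers: 210 × 0.80 = 168, or 84 per arm.
- Planned effect in SD of change: matching the noncentrality of the two-period interaction, f²·N·2/(1 − r), to that of a two-sample comparison of change, N·d²/4, gives d = √(4 × 0.01 × 2 / 0.38) = √0.2105 = 0.46.
- Assumed, not in the protocol: a (effect of singing on FDL change), b (FDL change to speech change) and c (direct effect of singing on speech), all in residual SD units.

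**Literal reading.** With speech change × group among the predictors of speech change, the added term was significant in 100% of 4,000 simulated trials, even with a = b = c = 0. Mean R² rose from 0.02 to 0.51. The comparison then carries no information.

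**Music × group reading.** Under full mediation, M = aG + e and Y = bM + u. The slope of Y on M is b in both arms, so the interaction is exactly zero whatever a and b are. Simulated rejection rates:

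| Scenario | Music × group interaction | Joint-significance mediation test |
|---|---|---|
| Full mediation (a = 0.5, b = 0.4) | 4.8% | 89% |
| Slopes differ by arm, a = 0 | 89% | 4.4% |

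The two tests answer different questions. The interaction is not the whole rule, however. With a = 0.8, b = 0.5, c = 0 and a significant speech effect, model 1 is kept in about 95% of trials by F test (90% by AIC), and its FDL slope is significant in essentially all of them.

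**Missing group term.** Set b = 0, so there is no mediation. Without group in the model, the pooled slope is Cov(M,Y)/Var(M) = (ac/4)/(1 + a²/4), where 1/4 is the variance of a 1:1 group indicator.
- a = 0.8, c = 0.46: 0.092/1.16 = 0.079. Residual variance is 1 + 0.46²/4 − 0.092²/1.16 = 1.0456, so SE = √(1.0456/(168 × 1.16)) = 0.073. Then z = 1.08, and the chance of exceeding 1.96 is about 19%.
- a = 0.5, c = 0.46: 0.0575/1.0625 = 0.054. Residual variance is 1.0529 − 0.0031 = 1.0498, so SE = √(1.0498/(168 × 1.0625)) = 0.077. Then z = 0.71, and the chance is about 11%.

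Simulation of the rule itself, given a significant speech effect, shows how often model 1 is chosen with FDL significant:

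| Content of model 2 | a = 0.8 | a = 0.5 |
|---|---|---|
| Interaction only, as stated | about 20% | about 11% |
| Interaction plus group main effect (F test) | 9.5% | 3.9% |
| Interaction plus group main effect (AIC) | 6.5% | 2.6% |
| For comparison: mediation test adjusted for group | 4.7% | 3.7% |

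In the second and third rows, model 2 is chosen in about 65-70% (F) or 79-84% (AIC) of trials. Its interaction then adds false positives at roughly the nominal 5%.

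**MINT.** H2 lists pitch, rhythm, timbre and higher-level skills. The test battery maps these to FDL, BAT, SMRT and MINT. The mechanism section uses the first three and gives no reason for dropping the fourth.

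**The case against.** The strongest reply is that this is mostly a slip of one noun in a cautiously worded, conditional analysis. Much of that stands. Music variables were almost certainly meant, so the literal result shows only that the sentence must be corrected. The planned group-by-session models for every macro measure supply the singing-to-music step, MINT included, and model 1 supplies a music-speech association. What remains missing is adjustment of that association for group, an indirect effect, and MINT in the second step.

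A reader might infer from the chance-level interaction that the plan would miss a true mechanism. The protocol does not support that. The rule reports the better-fitting model; under full mediation this is nearly always model 1, where the mediator shows as a significant slope. The 5% describes one coefficient, not the procedure.

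It is also fair to say that the false-contributor rate depends on an unstated term. The protocol's other models use the group * session form, which carries main effects. If model 2 follows that convention, the rate through model 1 falls to about 4-10%. The FDL shifts of 0.5 to 0.8 SD are assumptions, and smaller shifts give less inflation.

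Calling the analysis exploratory does not dispose of the point: the mechanism is stated under H2, outside the section on exploratory analyses.

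**Conclusion.** The point holds as a moderate one. The outcome on the predictor side, the absence of an indirect effect and the omission of MINT follow from the text alone. That a music × group interaction is zero under mediation with equal slopes is algebra and needs no assumed effect sizes. The consequence is that the comparison cannot separate mediation from association.

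The size of the false-contributor problem is conditional. It is about 11-20% if only the interaction is added and about 4-10% if model 2 also contains group, against about 5% for a group-adjusted mediation test. These figures assume 84 completers per arm, a 0.46 SD speech effect, FDL shifts of 0.5 to 0.8 SD and no mediation.

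The documents do not support reading this as a flaw in the trial's main results. The analysis follows a significant speech effect, and the H2 treatment-effect test, the sample size and data collection are untouched.

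**What to change.** Rewrite the section before outcome data are seen:

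1. Change speech perception variables to music perception variables in the interaction term.
2. Treat CRM change and EmoHI change as separate outcomes, and replace the closing reference to SIN change scores accordingly.
3. Regress each music change score (FDL, BAT, SMRT and MINT) on group.
4. Regress each speech change score on the music change scores plus group.
5. Report the indirect effect through each music measure with a bootstrap 95% confidence interval.
6. Keep music change × group only as a secondary check for effect modification, with the group main effect in the model.
7. State that the mediators are not randomised, so the music-to-speech step rests on no unmeasured confounding.

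The cost is rewording and a little extra analysis. No new data are needed, because MINT is already collected at both macro timepoints.
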